**Title:**

The Effect of Synbiotic Supplementation on Thyroid Hormones, Blood Pressure, Depression and Quality of Life in Hypothyroid Patients: A Randomized Double-Blind Placebo Controlled Clinical Trial

**Trial registration:**

IRCT20210926052583N1

**Protocol version:**

Version 1, October 2021

**Funding:**

Baqiyatallah University of Medical Sciences provides the financial funding for this research and no funding or sponsorship will be received from other institutions. The funder does not have any role in study design; collection, management, analysis, and interpretation of data; writing of the report; or the decision to submit the report for publication.

**Introduction**

**Background and rationale**

Hypothyroidism is a common endocrine disorder diagnosed with low levels of thyroid hormones, mainly due to the lack of thyroid hormone production by the thyroid gland or, secondarily, caused by the lack of thyroid stimulating hormone (TSH) from the anterior pituitary gland or thyrotropin-releasing hormone (TRH) from the hypothalamus (1, 2). Due to the vital role of thyroid hormones in metabolism, the clinical manifestations of this disease include fatigue, difficulty in concentration and memory, constipation, weight gain and loss of appetite, depression, slow heart rate and hypercholesterolemia (3). The prevalence of hypothyroidism is higher in women, but after the age of 60, its prevalence in men and women becomes ~10% (4). The incidence of hypothyroidism is reported to be 1-2% among two-thirds of the world's population living in communities with adequate consumption of iodine (5). The gold standard for treatment of hypothyroidism is currently dose-adjusted levothyroxine (6), although side effects such as neurological alterations have been reported from this drug (7). Because of the disease itself and its many complications, a great economic burden is imposed on the family and society (8), hence, the use of non-pharmacological methods with less complications and costs, in addition to the common treatment can be beneficial to the health care system and hypothyroid patients.

Probiotics are living non-pathogenic micro-organisms that, when received in sufficient doses, contribute to the health of the host; and prebiotics are degraded by these beneficial micro-organisms and enhance their growth or activity (9). The combination of probiotics and prebiotics with synergistic effects is called “synbiotic” (10). Modulating gut microbiota by synbiotic supplementation has shown to have beneficial health effects in various disease and conditions (11, 12).

Evidence suggests that there is an association between gut microbiota and thyroid function (13). Overgrowth of harmful bacteria in the gut can reduce the absorption of oral thyroxine and essential micronutrients for the thyroid gland, including iodine, iron, selenium, zinc and copper (14, 15). It is also suggested that the composition of the gut microbiota affects the metabolism of iodothyronines (precursor of thyroid hormones), and the intestinal-hepatic cycle of thyroid hormones (16, 17). Supplementation of probiotics in animal studies have shown contradictory results regarding thyroid hormones (18, 19), however, human experimental studies have mostly reported positive effect of probiotics on thyroid function (20, 21).

High blood pressure (BP) is relatively common in patients with hypothyroidism (22) and the effectiveness of probiotics in eliminating this risk factor has been approved by systematic review and meta-analysis studies (23, 24). Depression, another common complication of hypothyroidism, could be decreased by probiotic and synbiotic supplementation through reducing inflammation, modulating the gut-brain axis, and increasing serotonin level (25-27). It is also expected that synbiotic supplementation can enhance hypothyroid patients’ quality of life by balancing thyroid hormone and reducing depression (28).

Since synbiotics are a combination of probiotics and prebiotics and can more effectively modify the intestinal microbiota, it is expected that more positive effects of supplementation with synbiotics be observed in these patients. However, based on our best knowledge, only one clinical trial has investigated the effect of this nutritional therapy on hypothyroid patients so far (29).

**Objectives**

Primary Objectives:

Comparing the mean changes in serum levels of free thyroxine (FT4) and TSH as representatives of thyroid function, between the synbiotic and placebo groups and within the two groups before and after the intervention.

Secondary Objectives:

Comparing the mean changes in systolic blood pressure (SBP), diastolic blood pressure (DBP), depression, and quality of life between the synbiotic and placebo groups and within the two groups before and after the intervention. Also, other data including age, weight, height, body mass index (BMI), physical activity (PA), dietary energy and macronutrient intake, education, career, marital status, duration of the disease, dose of levothyroxine, and type of hypothyroidism (immune and non-immune-related) will be gathered to be taken into account as confounders.

Hypothesis:

10 weeks of synbiotic supplementation will significantly improve serum levels of thyroid hormones, depression, quality of life, SBP and DBP in hypothyroid patients.

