**Eligibility criteria**

Inclusion criteria

Women or men (25-55 years old) with subclinical hypothyroidism (elevated TSH level and a normal or low free T4 level) for at least a year, and BMI less than 35 who are being treated by levothyroxine. Voluntary written informed consent for all patients is mandatory before any study related procedures.

Exclusionary criteria

The participants must not have any of the following: lactating or pregnant; History of taking probiotic or synbiotic supplements in the last three months; Smoking or alcohol consumption; Taking appetite suppressants such as antibiotics; Use of antibiotics and any medications that interact with synbiotics; Gastrointestinal diseases such as stomach ulcers, diarrhea or constipation etc. for three months before or during the intervention; unwillingness to continue cooperation, non-compliance during the intervention, or no signed informed consent. Participants will also be excluded in case of providing incomplete questionnaires (more than 40% of the dietary questionnaire is incomplete), catching infectious diseases such as Covid-19 during the study, occurrence of pregnancy, undergoing surgery, occurrence of a change in the dose or type of medication, consumption of foods enriched with probiotics (e.g. probiotic yoghurt) during the study.

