**Interventions**

Therapeutic effect of probiotics and synbiotics on the serum level of thyroid hormones have been assessed with different species and doses of bacteria and follow-up duration between 4 to 12 weeks (30, 31). Previous trials have used either different species of Lactobacillus genus (32) or a combination of Lactobacillus and Bifidobacterium (21, 29-31, 33). The microbial load of the supplements varied between 10^7^ to 10^10^ CFU/g. Inulin, fructo-, and/or galacto- oligosaccharide have been used as the prebiotic component of synbiotic (21, 30, 32). We decided to conduct this intervention with synbiotic instead of probiotic, since the synergistic interaction of probiotic and prebiotic can more effectively improve the microbial composition of the gut and maintain the intestinal microbial balance (10). The duration of intervention was decided to be 10 weeks, as the previous trials with less duration of intervention reported no significant effect of synbiotic or probiotics on serum level of thyroid hormones and BP (29, 33). A comprehensive meta-analysis also showed that less than 8 weeks supplementation with probiotics had no significant effect on BP (34). The synbiotic supplement (Familact, 500 mg) that will be used in this study contains Lactobacillus casei, Lactobacillus acidophilus, Lactobacillus rhamnus, Lactobacillus bulgaricus, Bifidobacterium Breve, Bifidobacterium Longum, Streptococcus thermophilus plus fructo-oligosaccharide with microbial population of 10^9^ CFU/g. Placebos contain lactose, magnesium stearate, talc, and silicon dioxide and will be made in the same shape, color, odor and taste as the synbiotic supplements. Zist-takhmir Pharmacutical company will provide the synbiotic and placebo capsules. All participants will receive a capsule (Synbiotic supplement or placebo) to be consumed with lunch, daily. Also, the participants will receive appropriate recommendations regarding diet and PA. The recommendations will include: to follow a hypo-caloric diet; to avoid excessive intake of high-fat products (whole dairy products, poultry fat (the skin on chicken), processed meat, butter, cream, ice cream, and palm oil); to avoid excessive sugar intake (candy, soda, syrups, sugar-loaded desserts, caramels, chocolate); to increase PA by walking or cycling for at least 20 minutes for at least 5 days a week.

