**Recruitment**

The study will be advertised by printed flyers throughout the endocrine clinic of Baqiyatallah Hospital. Flyers will also be handed to practitioners caring for potential participants as well. All advertising material will have the contact number and email address of our research team on it, and interested patients will contact us directly if they wish to hear more about the trial and wish to schedule a telephone screen for eligibility assessment. Afterwards, the eligible and interested individuals will be asked to sign the written informed consent and the first appointment will be booked. During the first appointment, the consented subjects undergo a screening procedure to make sure they meet the inclusion criteria. The eligible subjects will be enrolled in the trial and randomized to appropriate study groups. The participant recruitment period is planned for 8 months and will continue until 56 patients are participated in the study.

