**Statistical methods**

Before statistical analysis, all data will be reviewed in terms of accuracy and completeness. Data will be analyzed using SPSS software (IBM Corp. Released 2016. IBM SPSS Statistics for Windows, Version 24.0. Armonk, NY: IBM Corp). For all analyses, a P value < 0.05 will be considered statistically significant. The normality of data will be checked by the Shapiro-Wilk W Test, P-P and Q-Q plots. All variables will be reported as mean ± SD for before, after the intervention and changes (after minus before). Baseline characteristics of quantitative biochemical and demographic variables will be compared between the two groups by independent sample t-test. The difference between the two groups regarding qualitative variables will be assessed by Chi-square test. Analysis of Covariance (ANCOVA) will be performed to eliminate the effect of confounders. Changes from the base-line to post-intervention within the groups will be illustrated through a paired t-test or Wilcoxon signed-rank test. GraphPad Prism software will be used to draw graphs and illustrate the results (GraphPad Prism version 8.0.0 for Windows, GraphPad Software, San Diego, California USA, [www.graphpad.com](http://www.graphpad.com)).

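### Within-group before/after tests stand inside the primary and secondary objectives, but a within-arm P value cannot show a synbiotic effect; only the between-group comparison can

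*Protocol*

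**What the plan says.** Protocol, Objectives: the primary objective compares mean changes in FT4 and TSH "between the synbiotic and placebo groups and within the two groups before and after the intervention". The secondary objective uses the same construction for blood pressure, depression and quality of life. Neither comparison is ranked above the other. The hypothesis reads "10 weeks of synbiotic supplementation will significantly improve serum levels of thyroid hormones", along with the secondary outcomes, and does not say relative to what.

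Protocol, Statistical methods: one significance threshold, 0.05, applies to all analyses. "Changes from the base-line to post-intervention within the groups will be illustrated through a paired t-test or Wilcoxon signed-rank test". This is the only sentence there that ties a named test explicitly to post-intervention change. The independent t-test is given for baseline characteristics, and ANCOVA is introduced only as a way of dealing with confounders.

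Protocol, Eligibility criteria: entry requires "subclinical hypothyroidism (elevated TSH level and a normal or low free T4 level) for at least a year", under levothyroxine treatment. Protocol, Recruitment: "During the first appointment, the consented subjects undergo a screening procedure to make sure they meet the inclusion criteria". The participant timeline (Figure 2) places both the eligibility screen and the primary outcome measurement at Day 0.

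Protocol, Interventions: "Also, the participants will receive appropriate recommendations regarding diet and PA". The content is a hypo-caloric diet, less fat and sugar, and more walking or cycling. The Follow-up box of the flow chart, by contrast, has the weekly contacts emphasise keeping the usual diet and activity.

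**The concern.** A change within the synbiotic arm is the sum of any synbiotic effect and everything else that happens over 10 weeks: regression to the mean, diet and activity advice, weekly contact, and time. The placebo arm is there to remove that second part, and a paired test in one arm does not use it.

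As written, a significant paired test in the synbiotic arm meets part of the primary objective and can be read as confirming a hypothesis that names no comparator. Setting a significant synbiotic arm beside a non-significant placebo arm is no better, because that pattern arises readily when the two arms change by the same amount. At stake is a claim of efficacy that the randomised comparison does not support.

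**Working it through.** **Inputs.** From the Sample size section: 24 evaluable patients per arm (28 randomised), alpha 0.05, and planning TSH changes of 0.08 (placebo) and 0.028 (synbiotic) mIU/L, each with SD 0.09. Two-sided testing is assumed because sidedness is not stated. The protocol gives no TSH cut-off, no test-retest correlation and no estimate of how far the advice moves any outcome; these are assumed below and shown over ranges. The 24 per arm is taken as given. It does not reproduce from the quoted figures (with SD 0.09, a difference of 0.28 needs 2 to 3 per arm and 0.052 needs 48), but that is a separate matter on which nothing here depends.

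**Step 1. Threshold.** With n = 24 the paired t-test is significant when |mean change| / SD of change exceeds t(0.975, 23) / √24 = 2.069 / 4.899 = 0.42.

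**Step 2. Shared shift, no synbiotic effect.** Let both arms move by δ SDs of change. The chance p that one arm's paired test is significant comes from the noncentral t distribution with 23 degrees of freedom and noncentrality δ√24. The arms are independent, so P(synbiotic significant, placebo not) = p(1 − p).

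| δ | p, n = 24 | p(1 − p), n = 24 | p, n = 28 | p(1 − p), n = 28 |
| --- | --- | --- | --- | --- |
| 0 | 5.0% | 4.8% | 5.0% | 4.8% |
| 0.2 | 15.6% | 13.1% | 17.5% | 14.5% |
| 0.3 | 29.1% | 20.6% | 33.4% | 22.3% |
| 0.4 | 46.7% | 24.9% | 53.2% | 24.9% |
| 0.5 | 65.0% | 22.7% | 72.3% | 20.0% |
| 0.6 | 80.4% | 15.8% | 86.4% | 11.7% |

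The product p(1 − p) cannot exceed 0.5 × 0.5 = 25%, so the row at 0.4 is the worst case and not a typical one.

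**Step 3. Regression to the mean in TSH, as one possible source of shift.** Take baseline as normal and truncated above c SDs, with baseline/follow-up correlation ρ. With λ = φ(c) / (1 − Φ(c)), the mean change is −(1 − ρ)λ. The SD of change is √[(1 − ρ)²v + 1 − ρ²], where v = 1 − λ(λ − c). For c = 1 and ρ = 0.7: λ = 1.525, v = 0.199, mean change −0.458, SD √(0.09 × 0.199 + 0.51) = 0.727, ratio −0.63, and p = 84% at n = 24. Other assumptions give:
- c = 1: 98% at ρ = 0.5, 66% at 0.8, 37% at 0.9.
- c = 0: from 53% (ρ = 0.5) down to 14% (ρ = 0.9).
- c = 1.96: from 100% (ρ = 0.5) down to 71% (ρ = 0.9).

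**Step 4. The between-group test under the same conditions.** A shift common to both arms cancels in the difference: (δ) − (δ) = 0. In 4,000 simulated trials with c = 1, ρ = 0.7, 24 per arm and no synbiotic effect, the false-positive rate was 5.1% for ANCOVA on baseline and 5.3% for the t-test on change. In the same trials the synbiotic-arm paired test was significant in 84%, and significant alone in 13%.

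**Step 5. The protocol's own planning figures.** A placebo change of 0.08 with SD 0.09 at n = 24 gives t = 0.08 / (0.09 / √24) = 4.35. If that is the true change, the paired test is significant with probability 98.6% in an arm that received no synbiotic. The synbiotic figure gives t = 0.028 / (0.09 / √24) = 1.52 (31%).

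**The case against.** The other side has several fair points.

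- The between-group comparison is named first, the design is randomised and placebo-controlled, and the sample size targets a between-group difference. The methods speak of illustrating within-group changes. Nothing says that efficacy will be concluded from a paired test. This stands, but it does not cure objectives that list both comparisons without rank, or a hypothesis without a comparator.
- Regression to the mean may be small. Entry describes elevation for at least a year, which suggests persistent elevation, and participants whose medication dose or type changes are excluded. The mechanism bears on TSH. It does not carry over clearly to FT4, which may be normal at entry, nor to blood pressure, depression or quality of life, which are not entry criteria.
- The planning placebo TSH change, if read as after minus before, is a rise, whereas regression from a high value predicts a fall. Step 5 therefore shows that an untreated arm can change significantly; it does not show regression to the mean.
- The diet and activity advice conflicts with the weekly message to keep to routine, so the advice may move the outcomes little.
- Large shifts make both arms significant, so the discordant pattern becomes less frequent: at p = 0.84 it is 0.84 × 0.16 = 13%.
- A statistical analysis plan, not shown, may say which comparison is confirmatory. That would help, but the objectives and hypothesis are fixed in the protocol and would still read as they do.

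A reader might go further and infer that a significant change in the synbiotic arm is to be expected even with no effect. The documents do not support that. It depends on a cut-off, a correlation and a shared shift that they do not give, and for regression to the mean alone the chance runs from about 14% to nearly 100%.

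**Conclusion.** The point holds in limited form. The objectives and the hypothesis allow an efficacy conclusion from a within-arm test, and such a test cannot show a synbiotic effect. With no shared shift its false-positive rate is 5%; with any shared shift it is higher. How much higher is unknown here, since the 0.2 to 0.6 SD range of shifts is assumed and not taken from the protocol. The randomised between-group comparison is not biased by shared shifts and remains a sound basis for the trial's conclusion. This is a correction of wording and of the role given to a test. It does not mean that the trial's main comparison is invalid.

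**What to change.** 1. In the primary and secondary objectives, delete the part on comparison within the two groups and keep the between-group part.
2. Add the comparison with placebo to the hypothesis.
3. In Statistical methods, state that efficacy is concluded only from the between-group difference with its 95% confidence interval, from ANCOVA adjusted for the baseline value of the outcome.
4. Report within-arm means and changes descriptively, without P values, in place of the paired t or Wilcoxon tests.
5. Reconcile the diet and activity recommendations in Interventions with the weekly message in the Follow-up box, so that it is clear what both arms are told.

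The cost is a few words in the objectives and methods. No data are lost and the sample size is unaffected. The one small loss is that within-arm P values can no longer be cited in support of efficacy.

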**Trial design**

We designed a double-blinded, randomized placebo-controlled clinical trial among patients with hypothyroidism. This will be a single-centered trial with a parallel design and a convenience sampling method.

**Methods: Participants, interventions, and outcomes**

**Study setting**

The study will be performed at the endocrine clinic of Baqiyatallah Hospital.

**Eligibility criteria**

Inclusion criteria

Women or men (25-55 years old) with subclinical hypothyroidism (elevated TSH level and a normal or low free T4 level) for at least a year, and BMI less than 35 who are being treated by levothyroxine. Voluntary written informed consent for all patients is mandatory before any study related procedures.

Exclusionary criteria

The participants must not have any of the following: lactating or pregnant; History of taking probiotic or synbiotic supplements in the last three months; Smoking or alcohol consumption; Taking appetite suppressants such as antibiotics; Use of antibiotics and any medications that interact with synbiotics; Gastrointestinal diseases such as stomach ulcers, diarrhea or constipation etc. for three months before or during the intervention; unwillingness to continue cooperation, non-compliance during the intervention, or no signed informed consent. Participants will also be excluded in case of providing incomplete questionnaires (more than 40% of the dietary questionnaire is incomplete), catching infectious diseases such as Covid-19 during the study, occurrence of pregnancy, undergoing surgery, occurrence of a change in the dose or type of medication, consumption of foods enriched with probiotics (e.g. probiotic yoghurt) during the study.

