**Outcomes**

Schedule of outcome assessment is represented in Figure 2. The primary outcomes include serum levels of TSH and fT4. The secondary outcomes are BP, quality of life, and depression. The information on anthropometric indices, PA, and dietary intake will be collected to control the potential confounders and covariates. The primary and secondary outcomes will be conducted at baseline and the end of the study (10th week) for all participants and change from baseline will be reported. Adherence will be checked every week.

**Figure 1**. Flow chart of the study design.

Eligible hypothyroid adults (women/men) with written informed consent will be recruited from Baqiyatallah hospital and will be enrolled in this RCT (n=56)

Randomize to two parallel treatment groups for 10 weeks (70 days):

1) synbiotic supplement (n= 28)

2) placebo (n= 28)

1

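### Entry requires levothyroxine treatment but no unchanged dose before Day 0, so drift from a recent dose change can be mistaken for within-group change and costs the between-group comparison power

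*Protocol*

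**What the plan says.** **Entry.** The inclusion criteria (Protocol, Eligibility criteria) ask for adults "with subclinical hypothyroidism (elevated TSH level and a normal or low free T4 level) for at least a year". The sentence runs on, "for at least a year, and BMI less than 35 who are being treated by levothyroxine", which makes current levothyroxine treatment a condition of entry. The duration attaches to the hypothyroidism. No minimum time on treatment, or on the current dose, is given there or elsewhere in the Protocol.

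**After entry.** The same section removes a participant for "occurrence of a change in the dose or type of medication, consumption of foods enriched with probiotics (e.g. probiotic yoghurt) during the study". This item stands among events that occur once someone is already taking part.

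**Look-back windows.** The section does look back before entry for other factors. It excludes "History of taking probiotic or synbiotic supplements in the last three months", and applies a three-month window to gastrointestinal disease as well. Levothyroxine dose has no such window.

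**Outcomes.** Under Outcomes, "The primary outcomes include serum levels of TSH and fT4", measured at baseline and week 10. The primary objective compares mean changes "between the synbiotic and placebo groups and within the two groups before and after the intervention", so the within-group change is a primary objective too.

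**Timing and covariates.** The schedule (Figure 2) puts eligibility screening, allocation and the first TSH and FT4 measurements on Day 0. Levothyroxine dose and disease duration are collected as possible confounders. The date of the last dose change is not.

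**The concern.** Levothyroxine is the treatment that acts most directly on both primary outcomes. By excluding participants whose dose changes during the study, the Protocol accepts that such a change disturbs the outcome. A change made shortly before baseline can have the same effect, because TSH and FT4 may still be settling during the 10 weeks. The Protocol guards one side of baseline and leaves the other open.

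Two things are at stake, and they differ in kind. Each arm's own before-after change could reflect an earlier dose adjustment instead of the capsule, and the paired test named under Statistical methods cannot tell the two apart. The between-group comparison would be noisier than planned, in a trial of only 28 per arm.

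**Working it through.** **Step 1. Does the text close the gap anywhere?**

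- *Inclusion criteria:* current treatment is required, with no unchanged-dose period.
- *Exclusion criteria:* a dose change counts only once the participant is in the study.
- *Figure 2:* screening and baseline fall on the same day. No run-in or repeat TSH before allocation could show stability.
- *Objectives and Statistical methods:* dose can enter an ANCOVA, but the dose on Day 0 does not show when it last changed. The model cannot adjust for a date that is not collected.

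Nothing closes it. A patient re-dosed days before Day 0 can meet every criterion as written.

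**Step 2. The plan's own sample size.** The Sample size section states α = 0.05, power 0.80, TSH changes of 0.08 and 0.028 mIU/L (each SD 0.09), a target of 0.28 mIU/L and 24 per group. The results below use a two-sample t-test; two-sided testing is assumed, since the section does not say.

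- Difference 0.08 − 0.028 = 0.052 with SD 0.09: 49 per group.
- Difference 0.28 with SD 0.09: 3 per group.

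Neither gives 24. At 24 per group, 80% power needs a standardised difference of 0.826, so a target of 0.28 implies SD = 0.28 / 0.826 = 0.339. That value is back-solved and does not appear in the Protocol. The mismatch is a separate matter; it matters here only because it leaves no firm SD to start from.

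**Step 3. Between-group illustration.** Let f be the share recently re-dosed and m their TSH drift over 10 weeks, in one direction. Both are assumptions. If f is the same in both arms in expectation, the expected between-group difference is unchanged and the SD of change becomes

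SD = √(SD₀² + f(1 − f)m²).

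For example, with SD₀ = 0.339, f = 0.20 and m = 1: √(0.339² + 0.20 × 0.80 × 1²) = √(0.115 + 0.160) = 0.524.

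Power for 0.28 mIU/L with 24 per arm, two-sided α = 0.05:

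| SD₀ | f | m (mIU/L) | SD | Power |
|---|---|---|---|---|
| 0.339 | 0 | – | 0.339 | 80% |
| 0.339 | 5% | 0.5 | 0.356 | 76% |
| 0.339 | 10% | 0.5 | 0.371 | 73% |
| 0.339 | 10% | 1 | 0.453 | 55% |
| 0.339 | 20% | 1 | 0.524 | 44% |
| 0.339 | 20% | 2 | 0.869 | 19% |
| 0.09 | 10% | 1 | 0.313 | 86% |
| 0.09 | 20% | 1 | 0.410 | 64% |

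**Step 4. Within-group illustration.** With no synbiotic effect at all, each arm's mean TSH change moves by f × m. That is 0.10 × 0.5 = 0.05, 0.10 × 1 = 0.10, 0.20 × 1 = 0.20 and 0.20 × 2 = 0.40 mIU/L. The comparison figures in the Protocol are 0.28 (target) and 0.052 (difference in the source trial). If doses were raised in some patients and lowered in others, part of this mean shift would cancel, but the added variance would not.

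The Protocol supports no corresponding calculation for FT4.

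**The case against.** The trial is randomised, double-blind and placebo-controlled. Dose changes before Day 0 precede allocation, so they are balanced between arms in expectation. A reader might infer that the treatment comparison partly measures dose titration, or that recently re-dosed patients could create a false difference. The Protocol does not support that. It is true that three more such patients in one arm of 24 would shift the difference by 3m/24, or 0.125 mIU/L at m = 1. But such chance imbalance is the same variability already counted in the larger SD. It enters the standard error, and type I error stays at its nominal level. This part of the objection stands in full: for the between-group contrast the harm is lost power.

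It is also fair that the size rests on assumption. The mild end of the table costs only a few points of power, the starting SD of 0.34 is back-solved, and the stated 0.09 gives much milder results. The source trial's SD may already contain some drift of this kind, in which case adding it again would overstate the loss.

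The likelihood of recent re-dosing is likewise inferred. Flyers are posted in the endocrine clinic and, under Recruitment, "Flyers will also be handed to practitioners caring for potential participants as well". Patients then contact the team themselves, are screened by telephone and book an appointment, which is not enrolment at a dose-adjustment visit. The elevated TSH in the inclusion criteria might also describe the diagnosis held for a year instead of the value on Day 0. It should not be taken as established that entrants are mostly patients in the middle of titration.

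None of this answers the within-group point. Randomisation does not protect a before-after change inside one arm.

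**Conclusion.** The gap is real and lies in the eligibility criteria, which the protocol itself fixes; it is not detail left to an analysis plan. As written, a patient re-dosed shortly before Day 0 can enter.

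Drift in such patients is directly confounded with the within-group change in TSH and FT4. For the between-group contrast it adds variance and lowers power, with neither bias nor type I inflation.

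The text supports the existence of the gap firmly. It does not support any particular size. The power figures depend on an assumed share, an assumed one-directional drift and a starting SD that the Sample size section does not settle. They show that the loss could run from slight to serious, and no more. The change is worth making because it is cheap and the co-treatment acts on both primary outcomes.

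**What to change.** Add to the inclusion criteria that levothyroxine dose and product have been unchanged for a stated period before Day 0, with baseline TSH and FT4 measured on that unchanged dose. The length of the period is for the investigators to set; the Protocol gives no basis for a particular figure. State in the same sentence whether the elevated TSH must be present at that measurement or describes the earlier diagnosis. Record the date of the last dose change among the baseline data. These changes affect who enters and when, not how anyone is treated.

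The cost is one eligibility sentence and one data field. The downside is that some patients would be deferred and re-screened, which may slow recruitment at a single centre with an 8-month window. If elevated TSH on the unchanged dose is required, the pool could shrink further. It might then also contain more patients due for an adjustment during the study, whom the existing exclusion would remove. The investigators should check the expected numbers before fixing the period.
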